##### Week 2: health through the lifespan

This module provides an overview of the biology of cancer, how cancer is defined, how cancer is treated, and the side effects of cancer treatments. Also reviewed are topics relevant to maintaining a healthy lifestyle over the lifespan including leading causes of mortality besides cancer, brain and mental health, and health screenings. At the conclusion of this module participants will be familiar with the leading causes of death and avoidable causes of death, the role of general health habits, the importance of health screenings, and the relevance of mind-body connections for health and cancer survivorship.

##### Weeks 3 and 4: nutrition

The first week of this module focuses on basic components of food such as carbohydrates, proteins, and fat. Whole grains, hydration, and caffeine are also discussed, as well as essential nutrients and dietary fiber. The second week provides an overview of healthy diet tips, serving sizes, and factors that contribute to unhealthy eating. Key topics in the second week include nutrition related to obesity, healthy serving sizes, nutritional “trade-offs”, healthy grocery shopping, and tips for maintaining a healthy diet. At the conclusion of this module participants will have an understanding of food components, as well as basic strategies to maintain good nutrition to promote health, including in cancer survivorship.

##### Week 5: physical activity

This module reviews the importance of physical activity in survivorship and also the importance of physical activity for the wellness of noncancer survivors across the lifespan. This module provides an overview and explanation of the basic components, principles, and health benefits of physical fitness. Information for developing and implementing a personal fitness plan and goals are also presented. The module concludes with practical tips for exercise, for example staying fit while traveling. It will also address the consequences of a lack of exercise (e.g., obesity), the health benefits of exercise (e.g., mental wellness, healthy aging, cardiovascular wellness), lactic acid, muscle burning and soreness, planning an exercise schedule, and exercise nutrition. At the conclusion of this module participants will have an understanding of exercise basics, the relationship between exercise and wellness, and how to better incorporate exercise in their own lives.

##### Week 6: sleep

This module provides an overview of the sleep cycle, the benefits of sleep, common sleep disorders, and tips for better sleep. Topics considered also include the neuroscience mechanisms of sleep, common sleep disorders, and tips for diet to promote healthy sleep, including for survivors. By the end of the module participants will understand the mechanisms of sleep, why sleep is important for good health (including in survivorship), and how to get better sleep.

##### Week 7: stress

This module reviews the concept of stress and how stress is known to impact health, including the biological mechanisms involved. Topics discussed include the definition of stress, a review of “America’s most stressed out cities”, types of stress (distress and eustress), negative effects of chronic stress, and basic ways to cope with stress. Of note, this module will not provide participants with a comprehensive stress management plan. Instead, the coping strategies for stress considered will be limited to general topics such as good sleep, physical activity, and diet (to synergize with earlier CHE modules).

##### Week 8: mental health and social support

This module provides a broad overview of mental health disorders (e.g., depression, anxiety disorders, eating disorders), as well as disorders that many survivors and caregivers experience. The health-related consequences of loneliness and the benefits of social interaction are also reviewed. This module also introduces the concept of social capital and explores the impact of social networking sites. By the end of the module participants will have a general understanding of mental health disorders and how social contact can promote wellness for survivors and caregivers.

### Power, data management plan, and analytic plan

As a preliminary effort, this study’s sample size was not determined based on power considerations. The goal is to estimate the effect sizes for the differences between the CBCT and CHE in the specified outcomes at weeks 9 and 13, so that the next definitive trial can be formally powered using the effect sizes estimated in this pilot study. Therefore, the sample size for this study (*n* = 40 dyads (80 participants total); CBCT *n* = 20, CHE attention control *n* = 20) is based on the number of cancer survivor-caregiver dyads projected to meet inclusion criteria and complete the entire study protocol in the study timeframe. The estimate of the effect size will be used to power the definitive trial, provided that the estimate falls into the range of clinically significant differences of 1/3 of the standard deviation or greater [62, 63]. The rigor of the proposed pilot randomized controlled trial design (i.e., having the CHE attention control) will secure the attribution of the effects to the intervention.

Questionnaire total scores, biomarker data, and other relevant endpoints (e.g., class attendance) will be entered into the study database and managed in SPSS (IBM Analytics, Armonk, NY, USA). Intervention fidelity will be summarized using the number of completed sessions.

For Aim 1 analysis (Hypothesis 1), acceptability will be measured by attendance at weekly classes. Acceptability will be determined as > 75% average attendance at weekly CBCT classes and > 75% average attendance at weekly CHE classes. For the other aims, both unadjusted and adjusted effect sizes will be estimated. Estimates of the unadjusted effect sizes will be computed as differences between sample means of two study groups at each time point divided by the pooled standard deviation. Furthermore, to reflect longitudinal design and inform planning of the larger definitive trial, we will estimate the effect sizes adjusted for repeated measures and inclusion of covariates. For Aim 2 analysis, two repeated measures of HRQOL outcomes will be entered into a linear mixed effects model with the following covariates: outcome measure at baseline, study group, time (week 9 or week 13), and group by time interaction. The least square (LS) means according to the levels of the interaction term will be output from the model, and effect sizes at each time point will be estimated as differences between the LS means divided by the adjusted standard deviation. Separate models will be fit for each survivor outcome and each caregiver outcome. We will use the same approach to estimate effect sizes for stress-related biomarker outcomes and associated hypotheses (Aim 3). A similar approach will also be employed in the analysis for Aim 4 to estimate effect sizes for healthcare utilization-related outcomes, except that generalized linear mixed effects modeling will be used for the analysis of two repeated measures, with the appropriate error distributions specified based on observed distributions of different health service use outcomes (counts of health services use, kept appointments, and patient activation).

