**Discussion:**

If CBCT shows acceptability, a larger trial will be warranted and appropriately powered to formally test the efficacy of this dyadic intervention. Interventions such as CBCT directed toward both survivors and caregivers may eventually fill a gap in supportive oncology care programs to improve HRQOL and healthcare utilization in both dyad members.

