Besides acceptability of CBCT and CHE, we will also evaluate effect sizes for the differences between CBCT and CHE on several outcomes especially relevant for survivors and caregivers. The primary outcome among these will be depressive symptoms, a key domain of psychological HRQOL. Secondary outcomes will include other HRQOL domains (anxiety, positive affect, fatigue, empathy, feelings of social connection), global HRQOL, dyadic function, and self-compassion. We will also assess stress-related biomarkers and healthcare utilization as secondary outcomes. Considerable evidence, including work by our group, suggests that HRQOL impairments in cancer survivors are causally linked to changes in stress-related physiological function, including diurnal cortisol production and biomarkers of inflammation (plasma interleukin (IL)-1β, IL-6, and tumor necrosis factor (TNF)-α; peripheral blood mononuclear cell (PBMC) nuclear factor-κB (NF-κB)) [37, 38]. HRQOL impairments (e.g., depression) have also been found to be associated with poor use of healthcare resources in cancer survivors [39]. The current trial will begin to extend our earlier findings with breast cancer survivors to survivors of other cancers, and CBCT will be conducted for the first time in a form where both cancer survivors and their caregivers take part in CBCT together. If CBCT and CHE are acceptable to survivors and caregivers, a larger trial in the future will be justified. To avoid the possibility of a floor effect with the outcomes assessed (especially psychological HRQOL; i.e., depression and anxiety), and because prior research with CBCT suggests brain systems implicated in compassion may show beneficial change when depression symptoms improve while learning CBCT [34], the study will enroll dyads with a survivor and/or caregiver with ≥ mild depressive and/or anxiety symptoms (according to PROMIS distress-depression or distress-anxiety four-item scales).

The overarching prediction of the current pilot trial is that participation in CBCT or CHE will be acceptable to solid tumor cancer survivors and their caregivers. We will also capture effect sizes for outcomes noted above for the comparisons of participants randomized to either CBCT or CHE. The following aims guide the pilot trial.

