### Study aims and hypotheses

Aim 1 is to demonstrate acceptability of CBCT and CHE for solid tumor cancer survivors and their caregivers. We predict that both CBCT and CHE will be acceptable for use with survivor-caregiver dyads, as reflected by > 75% average attendance at weekly CBCT classes, and > 75% average attendance at weekly CHE classes.

Aim 2 is to estimate effect sizes for the differences between CBCT and CHE at weeks 9 and 13 on HRQOL-related outcomes including outcomes of psychological HRQOL (depressive symptoms (primary outcome), anxiety, positive affect, and self-compassion), physical HRQOL (fatigue), and social HRQOL (empathy, feelings of social connection/isolation, dyadic function) as well as global well-being. Differences between groups at weeks 9 and 13 on HRQOL-related outcomes will be used to inform sample size calculations for a full-scale clinical trial.

Aim 3 is to estimate effect sizes between groups at weeks 9 and 13 on stress-related biomarkers of inflammation (plasma IL-6, IL-1β, TNF-α, NF-κB pathway activation), as well as diurnal saliva cortisol rhythm in survivor-caregiver dyads randomized to CBCT compared with survivor-caregiver dyads randomized to CHE. Differences between groups at weeks 9 and 13 on biomarker outcomes will be used to inform sample size calculations for a full-scale clinical trial.

Aim 4 is to estimate effect sizes for the differences between CBCT and CHE at weeks 9 and 13 on healthcare utilization (i.e., keeping appointments, use of preventive services, hospitalizations, and use of urgent care or emergency department services), and patient activation (i.e., motivation, knowledge, skills and confidence in managing personal health). Differences between groups at weeks 9 and 13 on healthcare utilization outcomes will be used to inform sample size calculations for a full-scale clinical trial.

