## Methods

### Study design, allocation procedures, and blinding

This interventional study uses a randomized controlled trial design to compare CBCT with CHE to determine effect sizes in study outcomes (see below). Participants review and sign the informed consent form in the presence of either the Principal Investigator or a study coordinator after a script is read aloud to them that describes the study. Enrolled dyads are randomized 1:1 in blocks of two dyads to either CBCT (*n* = 20 dyads) or the attention control (*n* = 20 dyads). CBCT and CHE groups are run concurrently. Group assignment to either CBCT or CHE is revealed after the baseline (T1) assessment is complete. This study protocol follows the Standard Protocol Items: Recommendations for Interventional Trials (SPIRIT) guidelines (see the SPIRIT checklist for this protocol in Additional file 1). Enrollment began in March 2018, and is recruiting at the time this report was prepared. We are running 3–4 cohorts of CBCT and 3–4 cohorts of the CHE group over 24 months, with 4–10 dyads in each cohort. HRQOL and healthcare adherence assessments as well as collection of biomarker samples are conducted before (T1), immediately after either 8-week intervention (T2), and then again 4–5 weeks later (T3). Overall study flow is depicted in Fig. 1. A study coordinator schedules assessment visits at the University of Arizona College of Nursing. Participants are also contacted the day before each assessment visit for a reminder, and to convey information about finding their way to the assessment site. If participants fail to complete study assessments at T2 (week 9), we attempt to collect data from them at T3 (week 13). Class attendance and at-home practice time (CBCT group only) are collected as measures of intervention engagement.

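### Sizing the definitive trial on the pilot's own effect estimate, and only when it reaches 1/3 SD, makes the planned size too small on average

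*Protocol article*

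**What the plan says.** The section 'Power, data management plan, and analytic plan' states that the pilot's "sample size was not determined based on power considerations". Its size comes from the number of dyads expected to be eligible and to finish: 40 dyads, 20 per arm. The section gives the goal as estimating effect sizes "so that the next definitive trial can be formally powered using the effect sizes estimated in this pilot study". It then adds a condition: "The estimate of the effect size will be used to power the definitive trial, provided that the estimate falls into the range". The range meant is 1/3 SD or more, which the authors treat as clinically significant.

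'Study aims and hypotheses' puts the purpose more softly for Aim 2: "Differences between groups at weeks 9 and 13 on HRQOL-related outcomes will be used to inform sample size calculations for a full-scale clinical trial". Aims 3 and 4 end with equivalent sentences for biomarkers and healthcare utilization.

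The analytic plan defines the unadjusted effect size as the difference in sample means divided by the pooled SD at each time point. It adds an adjusted version from a mixed model and fits survivors and caregivers separately. The article mentions no confidence bound, shrinkage or correction for selection in the step from pilot estimate to planning difference.

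**The concern.** Two features of the stated rule act together. The planning difference is a point estimate from a very small sample. It is also used only after it has cleared a threshold. An estimate kept because it is high is, on average, higher than the truth. Required sample size varies with the inverse square of the planning difference, so even a moderate overestimate shrinks the next trial considerably.

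Sizing the next trial is the purpose the article gives for Aims 2 to 4. A definitive trial planned this way could miss an effect of the size the authors themselves call clinically significant.

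**Working it through.** **Inputs from the article.** 20 dyads per arm; survivors and caregivers modelled separately, so at most 20 per arm in each estimate; threshold 1/3 SD.

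**Assumptions (the article gives none of these).** Definitive trial: two-sided 5%, 80% power, 1:1. True effect d: 0 to 0.8 SD. Pilot dropout: 0%, with 20% as a sensitivity case.

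The article has no power-based figure to reproduce, because the pilot's size was set by feasibility.

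**Step 1: precision.** SE ≈ √(2/20) = 0.316 SD. The 95% half-width is 1.96 × 0.316 = 0.62 SD. An estimate of exactly 1/3 has an interval of about −0.29 to 0.95.

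**Step 2: size needed for 1/3 SD.** n per arm = 2 × (1.960 + 0.842)² / d² ≈ 15.7 / d². At d = 1/3 this is 141.3, rounded up to 142. Every passing estimate is at least 1/3, so 142 per arm is also the largest trial the rule can produce.

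**Step 3: size of the bias, by hand.** If the true effect is 1/3, half the estimates pass. Under a normal approximation their mean is 1/3 + 0.316 × 0.798 = 0.59, where 0.798 is the mean of a standard normal variable above zero.

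**Step 4: simulation.** 1,000,000 pilots were drawn for each true effect (noncentral t, 38 df, times SE). Estimates of at least 1/3 were kept and each was put into the Step 2 formula. True power of the resulting trial is Φ(d/√(2/n) − 1.96). The last column uses any positive estimate, with no 1/3 SD condition.

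| True d | Passes | Mean passing estimate | Median planned n per arm | n needed | Mean true power | Same, any positive estimate |
|---|---|---|---|---|---|---|
| 0 | 15% | 0.51 | 73 | – | – | – |
| 0.2 | 34% | 0.55 | 61 | 393 | 21% | 53% |
| 1/3 | 50% | 0.60 | 52 | 142 | 42% | 65% |
| 0.5 | 70% | 0.67 | 40 | 63 | 62% | 71% |
| 0.8 | 93% | 0.86 | 23 | 25 | 75% | 76% |

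The planned n is below the needed n in 99.9% of passing pilots at d = 1/3, 71% at 0.5 and 53% at 0.8. Comparing the last two columns shows that noise alone costs power, and that the threshold adds materially to the loss unless the effect is large.

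**Step 5: sensitivity.** With 16 per arm (20% dropout) and d = 1/3, the mean passing estimate is 0.63, the median planned n is 47 and mean true power is 40%. Covariate adjustment does not remove the problem: in adjusted-SD units the SE at one time point is about the same.

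**Step 6: what if a failing pilot led to planning on 1/3 SD?** The article is silent, so this is an assumption. At d = 1/3, overall mean power would be 0.503 × 0.422 + 0.497 × 0.80 ≈ 0.61. At d = 0.5, 142 per arm gives about 99% power, so the overall mean is 0.702 × 0.615 + 0.298 × 0.99 ≈ 0.73. Both remain below 80%.

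**The case against.** The strongest reply is that the sentence governs only a future trial, which will need its own sample-size justification, and that the aims speak merely of informing that calculation. It is also true that the loss fades as the effect grows: at 0.5 SD about 29% of passing pilots still give an adequate size, and at 0.8 SD about 47% do. These points stand. They limit the severity but leave the direction of the bias unchanged.

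A reader might infer three stronger things that the article does not support.

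- *A worthwhile intervention would be dropped half the time.* The condition attaches to using the estimate for powering. Nothing says the larger trial is abandoned when the estimate is below 1/3 SD.
- *The rule contradicts the statements on progression.* The Abstract says "If CBCT shows acceptability, a larger trial will be warranted and appropriately powered", and the Background says "If CBCT and CHE are acceptable to survivors and caregivers, a larger trial in the future will be justified". Those sentences concern whether a larger trial is justified; the power section concerns which number sizes it. They can be read together.
- *The rule passes if any of several estimates passes.* The primary outcome yields survivor and caregiver estimates at two time points, but the article refers to one estimate and never says that any one would suffice. Which one is meant is detail that a condensed article may leave to the full protocol or analysis plan.

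**Conclusion.** The concern holds as a fault in a stated planning rule. An estimate with an SE of about 0.32 SD, used only if it is at least 1/3 SD, overstates the true effect on average, and the trial planned from it is too small on average. This holds at every true effect examined. The size of the shortfall depends on the unknown true effect: severe at or below 1/3 SD, moderate at 0.5 SD and small at 0.8 SD. The power figures rest on the assumed 5% two-sided level and 80% power and, except in Step 6, describe only pilots whose estimate passes.

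The point is worth correcting but is not critical, because the pilot's randomisation, data and own analyses are unaffected.

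**What to change.** Replace the conditional sentence in 'Power, data management plan, and analytic plan' with:

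> The definitive trial will be powered to detect 1/3 SD, the clinically significant difference. The pilot supplies the SD, the baseline/follow-up and within-dyad correlations, attendance and attrition. Pilot effect sizes are reported with 95% CIs and are not used as the planning difference.

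Bring the preceding statement of the goal in that section, and the closing sentences of Aims 2 to 4, into line. This is best done before the pilot's effect estimates are seen.

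The cost is wording, plus a less favourable planned size: about 142 per arm at 80% power (190 at 90%), before baseline adjustment, dropout and design effects. If the authors want to keep the pilot estimate as the planning difference, a conservative confidence bound or a selection-adjusted estimate would be the alternative. No pilot procedure changes.

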### Data handling

All study material including source documents and casebooks will be stored in a secured room at the University of Arizona College of Nursing or on a secure computer server or personal computer that are compliant with the United States Health Insurance Portability and Accountability Act (HIPAA) and that can only be accessed by study researchers. Data collected and study forms completed during assessment visits will be stored by study number, not by subject name. A paper copy list linking subject names to their subject numbers will be stored separately from all other study documents. Study materials including electronic data and study consent forms will be maintained for 6 years after the conclusion of the project. Aggregated results will be presented at professional conferences, published in appropriate scholarly journals, and provided to study participants upon request. The study Principal Investigator as well as co-Investigators will have access to the final study dataset, and no contracts are required to regulate this access.

### Data monitoring

It is possible that some of the participants may develop psychiatric and/or medical problems from screening to enrollment to after study end (up to 3 months later). Also, although not expected, it is possible that blood draws may result in adverse events for some participants. We have therefore elected to use the Data Safety Monitoring Board (DSMB) at the University of Arizona College of Nursing for this study. This DSMB will provide independent oversight to further promote the protection of human subjects and the overall integrity of the study. Once every 6 months, the DSMB will review a report from the study that includes: 1) the number of participants who signed consent for the study; 2) the number of dropouts; 3) reasons for these dropouts; 4) any safety concerns or adverse events (i.e., solicited and spontaneously reported adverse events and other unintended effects of trial interventions or trial conduct); 5) an up-to-date consent form; and 6) measures taken to protect confidentiality (e.g., data storage, use of coded ID numbers, etc.). After reviewing this information, the DSMB will issue its own report summarizing any serious and unexpected adverse events or other unanticipated problems that involve risk to study participants, and whether these appear related to the study-based research assessment protocol. Given the nature of the intervention and active attention control group, this study does not have a plan for interim analyses. Analyses guided by hypotheses noted above will only take place after all participants have completed the study protocol.

